### **Hypothesis:**

The BSMART intervention (SBIRT and varenicline) will

- i. Increase the proportion of smokers able to quit smoking
- ii. Increase the number of attempts to quit smoking
- iii. Increase the length of abstinence in failed quit attempts
- iv. Decrease the number of cigarettes smoked every day
- v. Decrease the number of days of using combustible products within the past month
- vi. Decrease the number of days of using combustible products within the past three months in people exposed to the intervention as compared to people in the control phase

**Potential Impact:** Addressing the syndemic between tobacco use and HIV infection in a coordinated manner aligns with the NIH HIV/AIDS priorities for effective cancer control among PLWH in a high HIV prevalence setting. This study is significant because it integrates smoking cessation interventions, which are lacking in sub-Saharan Africa (SSA), into a real-world HIV care system that has been underpinned by a robust PEPFAR/CDC program and leverages long-standing partnerships with Ministry of Health and Wellness and the University of Botswana's Anti-tobacco Network for population, health system, and policy level impact.

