### Follow-up

Research assistants will fill out follow-up smoking questionnaires at weeks 4, 12 and 24 after the patient receives the SOC brochure. Participants will be provided with breath CO measurements using CO Check+

(coVita) at baseline and then weeks 12 and 24 after enrollment. Participants will also be asked to respond to a semi-structured interview at week 24 that explores challenges to smoking cessation, barriers experienced by participants and reasons for success in those who were able to quit successfully.

| Table 2: Participant Timeline- Control Phase |                    |                                           |        |         |         |
|----------------------------------------------|--------------------|-------------------------------------------|--------|---------|---------|
|                                              | Responsible person | 1 st clinic visit/
Baseline | Week 4 | Week 12 | Week 24 |
| Screening of participants                    | LHW case manager   | X                                         |        |         |         |
| Informed Consent                             | Research Assistant | X                                         |        |         |         |
| Enrollment in BSMART study                   | Research Assistant | X                                         |        |         |         |
| Intake Smoking Questionnaire                 | Research Assistant | X                                         |        |         |         |
| Receipt of SOC brochure                      | LHW case manager   | X                                         |        |         |         |
| Follow-up smoking questionnaire              | Research Assistant |                                           | X      | X       | X       |
| Stages of change                             | Research Assistant | X                                         | X      | X       | X       |
| Breath CO                                    | Research Assistant | X                                         |        | X       | X       |
| Semi-structured Interview                    | Research Assistant |                                           |        |         | X       |

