### Provision of varenicline

Participants referred for treatment with varenicline will be taught the correct use of varenicline by the nurse prescriber/ dispenser (NPD) at the site where the participant receives care. Participants will initiate medication treatment with varenicline for smoking cessation with a quit date scheduled for day 8 following the first study dose of the medication. Participants will meet with the NPD at baseline who will evaluate them, provide medical clearance and sign off on prescription orders if they meet the requirements for varenicline use (See Appendix IX). Varenicline will be prescribed in accordance with package labeling and provided to participants by the nurse prescriber/ dispenser. Participants will receive a weekly supply of medication for the first four weeks to ensure proper dosing and monitoring for adverse events. For the subsequent eight weeks, participants will return every 4 weeks to receive the next month’s supply of medication. Dosage adjustments will be permitted in an effort to control adverse effects throughout the trial. This will allow us to balance internal validity with good clinical practice.

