Appendix B4: Follow-Up Smoking Questionnaire

**BSMART**

**Follow-up Smoking Questionnaire**

|                            |                        |
|----------------------------|------------------------|
| Researcher ID:      | Participant ID: |
| District:           | Facility:       |
| Date: (dd/mon/yyyy) |                        |

|                                                                                                                                                                                          |                                                                                       |                                                                                                                                                                                                                |
|------------------------------------------------------------------------------------------------------------------------------------------------------------------------------------------|---------------------------------------------------------------------------------------|----------------------------------------------------------------------------------------------------------------------------------------------------------------------------------------------------------------|
| 
Please answer these questions based on your experiences with smoking since the last time we saw you. When you select an answer, I will enter it on the form in the tablet.
 |                                                                                       |                                                                                                                                                                                                                |
|                                                                                                                                                                                          | Question                                                                       | Response                                                                                                                                                                                                |

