| 5. | 
Since your last study visit, have you ever quit for a period of at least 24 hours?
 
If No, skip to Q9.
                                                                                                                                                                                                                                                                                    |  Yes
 No                                                                                                                                                                                                                                                                                                   |
| 6. | 
Since your last study visit, how many times have you quit for at least 24 hours? (If more than 9 times, put 9)
                                                                                                                                                                                                                                                                                         | 
_____ times
                                                                                                                                                                                                                                                                                                                                            |
| 7. | 
After your most recent quit attempt, how long did you stay off cigarettes?
                                                                                                                                                                                                                                                                                                                             |  1-2 days
 A week
 2-4 weeks
 Over 4 weeks                                                                                                                                                                                                           |

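### The follow-up questionnaire counts quit attempts since an undefined last study visit; read literally, this shortens the look-back for varenicline users at weeks 4 and 12 and misses their scheduled day-8 quit date

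*Protocol*

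**What the plan says.** Appendix B4 opens with the instruction "Please answer these questions based on your experiences with smoking since the last time we saw you". Item 5 asks whether the participant has quit for at least 24 hours since the last study visit, with the routing "If No, skip to Q9". Item 6 is the count: "Since your last study visit, how many times have you quit for at least 24 hours". Item 7 asks how long the most recent attempt lasted and carries no visit anchor of its own. A No at item 5 bypasses items 6, 7 and 8.

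In the control phase (Participant Timelines - Control Phase, Follow-up), "Research assistants will fill out follow-up smoking questionnaires at weeks 4, 12 and 24". Table 2 shows no contact between those weeks. Table 3 gives the same questionnaire weeks for the intervention phase, but varenicline users are seen in between: "Participants will receive a weekly supply of medication for the first four weeks to ensure proper dosing and monitoring for adverse events", and then every four weeks. The adherence form lists weeks 1, 2, 3, 4, 8 and 12. The same section sets the quit date at day 8 after the first dose.

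Hypothesis ii is "Increase the number of attempts to quit smoking", and hypothesis iii concerns length of abstinence in failed attempts. Quit attempts, and the length of each, are listed secondary outcomes. For this questionnaire, Estimating process and outcome measures (item 4) measures longest abstinence from the last evaluation, which is a different anchor from the one on the form.

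**The concern.** A count of events is comparable between phases only if it is taken over the same period. Here the form and its weeks are the same in both phases, but the start of the look-back depends on when the participant was last seen, and treatment with varenicline adds contacts. The more closely a participant is followed for medication, the shorter the period asked about. The weeks that drop out include the day on which the protocol itself schedules the quit attempt.

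At stake are hypotheses ii and iii. A difference in recorded attempts between phases could partly reflect the calendar of pick-ups rather than behaviour. Because item 5 also controls access to item 7, an attempt missed at item 5 loses its duration as well.

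**Working it through.** The plan states no figure on this point, so there is none to reproduce. The check is calendar arithmetic.

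**Inputs**
- Questionnaire weeks: 4, 12, 24 (Tables 2 and 3).
- Control contacts: weeks 0, 4, 12, 24 (Table 2).
- Contacts for varenicline started at baseline: weeks 0, 1, 2, 3, 4, 8, 12, 24 (Provision of varenicline; adherence form).
- Intervention participants not on varenicline: weeks 0, 4, 12, 24.
- Quit date: day 8.

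**Look-back windows on the literal reading**

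Window = questionnaire week − latest earlier contact.

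| Questionnaire | Control, or no varenicline | Varenicline from baseline |
|---|---|---|
| Week 4 | 4 − 0 = 4 weeks (days 0–28) | 4 − 3 = 1 week (days 21–28) |
| Week 12 | 12 − 4 = 8 weeks (days 28–84) | 12 − 8 = 4 weeks (days 56–84) |
| Week 24 | 24 − 12 = 12 weeks (days 84–168) | 24 − 12 = 12 weeks (days 84–168) |
| Total | 24 of 24 weeks | 17 of 24 weeks (17/24 = 0.71) |

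In the first 12 weeks the coverage is 12/12 against 5/12 (42%). Table 3 also marks adverse-event checks at weeks 5 to 7; including them changes nothing, because week 8 is still the last contact before week 12.

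**Where day 8 falls.** It is inside days 0–28 for controls. It is before day 21, so in none of the varenicline windows.

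**Later starts.** If the first dose is in week s and the pick-up calendar shifts with it, the quit day is 7s + 8. For s from 0 to 12 it falls in a window only when s = 2 (day 22, window days 21–28) or s = 10 (day 78, window days 77–84).

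**What is lost**
- Quits on day 8, relapses before day 21, does not retry: No at item 5 in week 4. The failed attempt, of up to 21 − 8 = 13 days, is recorded neither as a count nor as a length.
- Quits on day 8, still abstinent at week 4: has been off cigarettes for more than 24 hours since week 3, but started no new quit. Yes and No are both defensible answers.

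**Size.** Assume the same constant attempt rate in both phases and let u be the share of intervention participants on varenicline from baseline. The expected ratio of recorded attempts, intervention to control, is R(u) = 1 − u × (1 − 17/24).
- u = 0: R = 1.00
- u = 0.5: R = 1 − 0.5 × 0.292 = 0.85
- u = 1: R = 0.71

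At u = 1 the true rate would have to be 24/17 = 1.41 times the control rate for equal counts to be recorded.

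**If only questionnaire visits count.** With contacts at weeks 0, 4, 12 and 24 for everyone, the windows are 4, 8 and 12 weeks in both phases and day 8 is inside the week-4 window.

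**The case against.** The strongest reply is that a study visit may mean only the research assistant's visit. The Semi-structured Interviews section uses the term for the week-24 assessment. Estimating process and outcome measures (item 7) calls pick-ups medication visits. Tables 2 and 3 give the questionnaire to the research assistant and the in-between contacts to nurse prescribers. The person reading "since the last time we saw you" aloud is the one entering the answers. The last-evaluation wording also fits equal windows.

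This stands as a possible reading, so one should not infer that the windows simply are 1 and 4 weeks. It does not dispose of the point. Referral to treatment has the study team supplying the drug and the study clinician checking for adverse events. Item 8 of the measures section treats these as study contacts. Appendix H costs travel for follow-up visits on the pick-up calendar. A participant asked at week 4 could naturally think of week 3, and the doubt arises only for those on treatment.

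Three stronger inferences are not supported:
- That every intervention-phase window misses the quit date. Participants not on varenicline keep the control windows, and the week-24 window is equal for all.
- That the missed attempts are wholly unrecoverable. The staging form, given at baseline and weeks 4, 12 and 24 in both phases, asks smokers how often they quit for 24 hours in the last year. It is a partial substitute: it mixes in attempts from before enrolment, gives no durations, and is not asked of those who have stopped.
- That a true increase would be reversed. This depends on uptake, on how staff read the anchor, and on the true attempt rates, none of which the protocol gives.

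**Conclusion.** The concern holds as a measurement problem in secondary outcomes. As worded, the form permits, and on its literal reading produces, a shorter look-back for varenicline users at weeks 4 and 12, and it omits the scheduled quit date for those who start at baseline.

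For the number of attempts the bias runs against the intervention, with a recorded ratio between 1.00 and 0.71 depending on uptake (0.85 at an assumed 50%). These figures rest on pick-ups counting as study visits, treatment starting at baseline, and a constant attempt rate that is the same in both phases. A real concentration of attempts around day 8 would not follow that rate, so the ratios illustrate the scale and do not predict it.

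Length of attempts is affected only through a No at item 5. That bias is also against the intervention if a participant with no recorded attempt counts as having no abstinence; a mean over recorded attempts alone could behave differently, because the attempts lost are short.

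A reader might infer that the trial's main result is at risk. It is not: the primary outcome is CO-verified 7-day abstinence at six months and does not use these items. The change should be made, but the validity of the primary comparison does not depend on it.

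**What to change.** - In the Appendix B4 header and items 5 and 6, replace the visit anchor with the date of the participant's previous smoking questionnaire; at week 4, use the enrolment date. Have REDCap pre-fill that date.
- State on the form and in training that medication pick-ups do not reset the window.
- State that a quit still in progress counts as Yes at item 5, so that item 7 is answered.
- Use the same anchor in item 4 of Estimating process and outcome measures.

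Both phases then have windows of 4, 8 and 12 weeks, covering 24 of 24 weeks, and day 8 falls in the week-4 window.

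The cost is a wording change, one pre-filled date field and a short training note. The drawback is somewhat longer recall for varenicline users (4 weeks instead of 1 at week 4, 8 instead of 4 at week 12), which is what controls already have.

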#### Secondary Outcomes:

- Quit attempts
- Length of successful quitting during each attempt
- Number of cigarettes currently smoked, and
- Number of days of using combustible tobacco products for at least 24 hours within the past month and the last 3 months.

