### Estimating process and outcome measures

All procedures will be conducted according to the local standards of routine clinical care. The following measures will be utilized:

1. **Baseline Demographic Information:** Baseline information will be abstracted from the HIV medical records and collected using a questionnaire. Baseline information will include demographics, medical history, laboratory values measured as part of HIV care (e.g. viral load, CD4), antiretroviral (ARV) history and ART treatment regimen (for current patients), and ART treatment start date. Because of high viral load suppression and high retention rate in this population, we will not be analyzing HIV treatment variables as mediators or outcomes.
2. **5”A”s (SBIRT) checklist:** This checklist will be completed by the LHW case managers and will serve to document the delivery of the intervention. A 10% random sample of the completed 5”A”s checklist will be reviewed by [name] during the time that a site is engaged in the intervention to ensure fidelity to the study intervention.
3. **Intake Smoking History Questionnaire** will measure length of smoking, use of other tobacco products, quit attempts, length of longest quit attempt, and smokers in the immediate living environment.
4. **Follow-up Smoking Use Questionnaire** will measure 7-day and 30-day point prevalence abstinence, number of cigarettes smoked (if not abstinent), stage of change and readiness to quit (if not abstinent), length of longest period of abstinence since last evaluation, use of varenicline, side effects, reasons for using or not using varenicline, and length of varenicline use.

5. **Stages of Change Algorithm** and **the Readiness Ruler**, will be used at baseline and follow-up to determine each individual's stage of change for quitting tobacco.
6. **Smoking Abstinence**: Abstinence will be based on self-reported 7-day point prevalence abstinence confirmed by expired CO < 6 ppm. Abstinence criteria must be met in participant Month 6 or at an earlier study week and maintained through participant Month 6 to be considered a responder. We will use coVita CO Smokerlyzer, a single-breath point-of-care tool designed specifically for use in smoking cessation programs and clinics.

For those who agree to be treated with varenicline:

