| 6.                                                            | After your most recent quit attempt, how long did you stay off cigarettes?                                                                                                                                                                                           |  1-2 days
 A few days
 A week
 Two to four weeks
 More than four weeks |
| I will now ask you a few questions about your smoking history |                                                                                                                                                                                                                                                                      |                                                                                                                                                                                                            |
| 7.                                                            | To the best of your knowledge, categorize the use of cigarettes by the following people in your life                                                                                                                                                                 | 1 = Smoker
2 = Ex-smoker
3 = Never smoked
4 = Not applicable                                                                                                                                      |
|                                                               | 
 
▪ Father
 
▪ Mother
 
▪ Spouse
 
▪ Best friend
 
▪ Closest work associate
 
                                                                                                              | 1   2   3   4
1   2   3   4
1   2   3   4
1   2   3   4
1   2   3   4                                                                                                                          |

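### The follow-up question on how long the last quit attempt lasted has no answer for 3–6 or 8–13 days, yet it is the form's only measure of attempt length

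*Protocol*

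**What the plan says.** The protocol lists "Length of successful quitting during each attempt" among its secondary outcomes. The third item under Hypothesis is that the intervention will "Increase the length of abstinence in failed quit attempts", and the list closes by stating the contrast: "in people exposed to the intervention as compared to people in the control phase".

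At follow-up, Appendix B4 first asks "Since your last study visit, have you ever quit for a period of at least 24 hours" (Q5). Those who answer yes are then asked "After your most recent quit attempt, how long did you stay off cigarettes" (Q7), with the options "1-2 days A week 2-4 weeks Over 4 weeks".

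At intake, Appendix B3 Q6 asks about the most recent attempt in the same terms, with the options "1-2 days A few days A week Two to four weeks More than four weeks".

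The section Estimating process and outcome measures says that the follow-up form captures "length of longest period of abstinence since last evaluation". No item on Appendix B4 asks for that. Q1 and Q2 record only whether the participant smoked in the past 30 and 7 days, and Q6 counts attempts.

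**The concern.** A closed list of durations should let every respondent find one correct answer. Here a participant who stayed off cigarettes for 4 or 10 days has no matching option and has to be placed in a neighbouring one.

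The short lengths matter most for the hypothesis on failed attempts, since attempts that ended within two weeks are among those it concerns. Q5 admits any attempt of at least 24 hours, so these lengths are within scope. What was never recorded cannot be rebuilt from the other items, so this is not something an analysis plan could repair. At stake is the quality of one secondary outcome and one hypothesis.

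**Working it through.** No sample size, power or error-rate figure is involved, and the protocol states no figure to reproduce. The check sets the two option lists side by side and counts whole-day durations. The labels are read literally: *A week* as 7 days, *2-4 weeks* as 14–28 days, and the intake form's *A few days* as 3–6 days.

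| Length of attempt | Follow-up (B4 Q7) | Intake (B3 Q6) |
|---|---|---|
| 1–2 days | has a box | has a box |
| 3–6 days | none | has a box |
| 7 days | has a box | has a box |
| 8–13 days | none | none |
| 14–28 days | has a box | has a box |
| over 28 days | has a box | has a box |

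**Follow-up.** Days 3–6 give 4 uncovered values and days 8–13 give 6. The total is 4 + 6 = 10, all within the first 13 days, so 10 of 13 short durations have no box (10 of the first 28).

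**Intake.** Only days 8–13 are uncovered, which is 6 values. The difference between the forms is therefore the 3–6 day band alone. From two weeks up, the lists agree.

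**Effect on one answer.** A 4-day attempt is entered either as 1–2 days (at most 2/4 = 0.5 of the true length) or as a week (7/4 = 1.75 times). A 10-day attempt is entered as a week (7/10 = 0.7) or as at least two weeks (14/10 = 1.4).

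**Looser reading of *A week*.** If respondents use it for 6–8 days, the uncovered days are 3–5 and 9–13, which is 3 + 5 = 8 of 13. If they use it for 5–9 days, they are 3–4 and 10–13, which is 2 + 4 = 6 of 13. The gaps narrow but do not close.

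**Partial repair.** Adding the intake form's few-days option to Q7 would cut the uncovered days from 10 to 6 and make the two lists match. The 8–13 day gap would remain on both forms.

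**Outcome against item.** The secondary outcome refers to each attempt, the methods section to the longest abstinent period since the last evaluation, and Q7 to the most recent attempt. When Q6 records more than one attempt between visits, these are three different quantities, and only the last is collected.

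**The case against.** Banded durations are a legitimate choice, and a top band of over four weeks is a matter of granularity, not an error. Respondents will also round: many would call 8 or 9 days a week. That stands, but the protocol gives no rounding rule, so the rounding is uncontrolled.

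Three stronger readings are tempting and are not supported.

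*Follow-up cannot be compared with baseline.* The mismatch is confined to the short bands. The stated contrast is intervention against control phase, with the same follow-up form used in both. Statistical Analysis for Study Objective 1 describes no change from baseline in attempt length. The recall windows differ in any case, because the follow-up items refer to the time since the last visit.

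*Unblinded research assistants pick the wrong box, so the error differs by phase.* The instruction at the top of Appendix B4 has the participant choose the answer and the assistant enter it. Participants also know their phase. Varenicline users have a quit date on day 8 that controls do not have, so the spread of lengths at the week 4 visit could differ. A phase-dependent error is therefore possible, but nothing in the protocol shows one.

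*A large share of attempts is misclassified.* The protocol gives no distribution of attempt lengths. One can assume a constant relapse risk after the first 24 hours, with the median counted from that point, and take *A week* as 7 to under 8 days. The share is then P(3 to <7 days) + P(8 to <14 days), where P(length ≥ t) = 2^(−(t−1)/m). For m = 7 this is (0.820 − 0.552) + (0.500 − 0.276) = 0.49. For m = 4, 14 and 28 it is 0.55, 0.34 and 0.21. These figures depend wholly on the assumed model and on the strict reading of a week. They also ignore participants who are still abstinent at the visit. They illustrate the issue and do not estimate its size.

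**Conclusion.** The form defect is real. Follow-up Q7 has no answer for 3–6 or 8–13 days, which is 10 of the first 13 whole-day durations on a literal reading and 6 to 8 of 13 on the looser readings tried above. It is the only follow-up item on attempt length. The secondary outcome and the hypothesis on failed attempts would therefore be compared between phases on arbitrarily rounded data.

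The consequence is limited. What is shown is coarse measurement, not bias between phases. The disagreement with intake affects only the short bands and no analysis planned in the protocol. The proportion of attempts affected is unknown. The primary outcome, CO-verified 7-day abstinence at six months, does not use this item. This is a minor point, worth correcting because it is cheap and because lengths not recorded are lost.

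**What to change.** Record the number of days abstinent in Appendix B4 Q7 and Appendix B3 Q6, and derive categories afterwards. If bands are preferred, use one identical set without gaps on both forms, for example 1–2 days, 3–6 days, 7–13 days, 2–4 weeks (14–28 days) and over 4 weeks.

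If follow-up forms have already been completed, keep the old options on the form alongside the day count. Table 1 places the control year before the implementation year at every facility, so replacing the item mid-trial would tie the form version to the phase. Keeping the old answers lets both phases be analysed on the same bands.

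Separately, reconcile the three definitions. Either the secondary outcome and the methods text should refer to the most recent attempt, or the form should collect what they name. Changing Q7 to days does not settle this.

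The cost is a small REDCap edit on two forms, plus a wording change in the protocol. Forms already completed, at intake or follow-up, stay banded.
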